## Abstract

**Background::**

Clinical and basic research supports that blood glucose fluctuation is an important predictor of diabetic vascular disease and an etiology of lower extremity atherosclerosis, which is an important pathological basis for lower extremity vascular diseases. Previous Chinese National Natural Science Foundation trials (No. 81503566) have reported that the traditional Chinese medicine Shenqi compound can reduce blood glucose fluctuation and low-grade inflammation, and protect blood vessels; however, there are no high-quality clinical evidences available to support the same. This multicenter randomized controlled trial aims to obtain more clinical evidence to confirm the efficacy and safety of Shenqi compound in type 2 diabetes with lower extremity atherosclerosis.

**Methods::**

A multicenter RCT will be implemented in this study for a 32-week study period (8 weeks for intervention and 24 weeks for follow-up). Participants will be recruited from the Teaching Hospital of Chengdu University of TCM, Mianyang Hospital of TCM, and Shuangliu Hospital of TCM. Sixty participants will be randomly divided into a treatment group (basic treatment combined with traditional Chinese medicine Shenqi Compound) or a control group (basic treatment combined with Chinese medicine placebo) with 30 participants in each group. Patients will be selected considering the following inclusion criteria: age between 35 and 65 years, and a positive diagnosis for type 2 diabetes with lower extremity atherosclerosis and TCM syndromes. Primary outcome indicator is an arterial color Doppler ultrasound. Secondary outcome indicators include: blood glucose fluctuation indicators (MBG, SDBG, LAGE), islet β-cell function evaluation indicators (Homa-IR, Homa-islet, SG, SCP), inflammation indicators (NLR, CRP, IL-6), blood lipids, and HbA1c. Safety index includes vital signs (T, P, R, BP), blood, urine, stool routine, liver and renal function, electrocardiogram, and adverse event records. The endpoint event is defined as the presence of gangrene in the lower limbs.

**Discussion::**

Explore the clinical effect of traditional Chinese medicine “Shenqi Compound” to reduce blood glucose fluctuation and use HOMA-IR, the area under the glucose curve, and the area under the C-peptide curve to evaluate the effect of protecting islet β cell function.

**Trial registration:**

: Chinese clinical trial registry (ChiCTR-1900027693). Registered on November 23, 2019. http://www.chictr.org.cn

## Lower extremity atherosclerosis is an important pathological basis for vascular disease

2

Artherosclerosis (AS) is a vascular disease characterized by arterial intimal lipid deposition and calcification (plaque formation). There are generally no clinical symptoms in the early stages of the condition; however, the later stages demonstrate the presence of vascular occlusion and bilateral lower extremity ulcers. Type 2 diabetes with lower extremity atherosclerosis is the main cause of secondary foot ulcers and lower limb amputations in patients with diabetes, and is also a risk factor for coronary heart disease and cerebral infarction.^[6,7]^ Lower extremity arteries are prone to atherosclerosis due to their thickness and length, along with high blood pressure and endometrial injuries. Ultrasound is one reportedly of the first choices for the early diagnosis of lower extremity arterial disease in type 2 diabetes.^[8]^ It can observe a variety of indicators including the diameter of blood vessels, plaque distribution, and stenosis; furthermore, it judges the severity of lesions and provides a basis for treatment and prognosis.

## Research basis of Shenqi compound and its unique hypoglycemic advantages

3

Shenqi compound has been used in clinical settings for 16 years. It was initially mass produced internally in the Teaching Hospital of Chengdu University of TCM in 2016. It has been used in 19 medical institutions in 19 districts (cities), counties, and high-tech zones within Sichuan province. Currently, it has been included in the “Diabetic Clinical Diagnosis and Treatment Program” of the National TCM Clinical Research (Diabetes) Base.

Previous research by the research group has confirmed that Shenqi compound can regulate glucose and lipid metabolism disorders, improve vascular function, and effectively prevent and treat diabetic vascular disease.^[9]^ In 2015, the National Natural Science Foundation of China (No. 81503566)^[10]^ found that it can regulate serum insulin level, inhibit mTOR activation and autophagy, and regulate the circadian clock Id2 and Usp2 genes of the pancreatic tissue to stabilize blood glucose. Comprehensive evaluation, Shenqi compound has multiple effects of reducing blood glucose fluctuation, reduces low-level inflammation, protects blood vessels, subsequently providing a research basis for this subject.

## Methods

4

### Objective

4.1

To compare the efficacy on reducing blood glucose fluctuation and improving lower extremity atherosclerosis of patients with type 2 diabetes of a combination of acarbose and insulin detemir, along with the effects of basic treatment of traditional Chinese medicine Shenqi compound.

### Research type

4.2

Randomized controlled multicenter trial.

### Screening of participants

4.3

The trial will be conducted at the Teaching Hospital of Chengdu University of TCM, Mianyang Hospital of TCM, and Shuangliu Hospital of TCM.

### Groups

4.4

Participants will be divided into two groups: the treatment and control groups. Their basic treatment can maintain the original plan, which includes a hypoglycemic regimen comprising acarbose + insulin detemir, along with antihypertensive drugs, such as ACEI, ARB, diuretics, calcium antagonists, and β-blockers. Following which lipid-lowering drugs like atorvastatin will be administered.

Control group: Basic treatment + Chinese medicine placebo.

Treatment group: Basic treatment + Shenqi compound. One bag of the test drug three times a day, boiled with water before meals, stirred, covered, and sealed for 3 to 5 min, for a period of 4 weeks. Followed by observation for 8 weeks.

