#### Secondary outcomes

4.8.2

1.Measurement of blood glucose levels before three meals, 2 h after three meals, and before sleeping; calculation of average blood glucose levels (MBG), standard deviation of mean blood glucose (SDBG), and maximum blood glucose fluctuation (LAGE).2.β-cell function evaluation index: insulin resistance index (HOMA-IR), area under the glucose curve (SG), and area under the C-peptide curve (SCP). Calculating HOMA-IR, SG, and SCP by:Homa-IR (CP) = 1.5 + G 0 min × CP 0 min/2800; Homa-islet (CP) = 0.27 × CP 0 min/(G 0 min − 3.5);SG = (G 0 min + G 180 min)/2 + G 30 min + G 60 min + G 120 min;SCP = (CP 0 min + CP 180 min)/2 + CP 30 min + CP 60 min + CP 120 min;(G 0 min to G 180 min, CP 0 min to CP 180 min, respectively means blood glucose and C-peptide values at each time point after Steamed bun test).^[18,19]^Blood glucose will be tested at visits 1, 3, and 5. β-cell function evaluation index will be tested at visits 1 and 5.3.Blood lipid: total cholesterol (TC), triglyceride (TG), high density lipoprotein cholesterol (HDL-C), and low density lipoprotein cholesterol (LDL-C);4.Inflammation indicators (NLR, IL-6, and CRP)5.HbA1c

Blood glucose will be tested at visits 1, 3, and 5. β-cell function evaluation index, HbA1c, inflammation indicators and blood lipid will be tested at visits 1 and 5.

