#### Clinical examination

4.9.1

Before the start of the trial, a history of diabetes, current medication, other medical history, and treatment history will be recorded. The anthropometric data will be collected at five time points (baseline, w4, w8, w12, w24), will be collected using standardized inspection procedures including: gender, age, height (shoes removed), weight (after morning urine, fasting status), body mass index (BMI), waist circumference (perimeter of the horizontal plane at the midpoint of the axillary midline from the rib arch to the midpoint of the crotch margin), hip circumference (largest possible hip circumference), waist-to-hip ratio (WHR). Measure vital signs including blood pressure, heart rate, breathing, and temperature.

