#### Statistical analysis method

4.9.8

We will use the SPSS20.0 software for statistical analysis of the experimental data. Measurement data will be tested by *t* test, expressing as mean ± standard deviation. Paired design *t* test may also be used for intra-group comparisons. The chi-square test will be used for the enumeration data. Rank-sum test will be used for rank data. The comparison of survival rate and survival time between the two groups will be analyzed by Kaplan–Meier curve.

The analysis data set will be selected from the following:

1.Full analysis set (FAS): Including all subjects who received at least one treatment after randomization and having more than one follow-up record. If the case fails to complete the treatment course, the final observation should be implemented instead. The number of subjects who will undergo evaluation for the efficacy at the end point should be the similar to that at the beginning of the trial.2.Per protocol (PP): In accordance with the treatment protocol, the main variables can be determined, and there is no major violation of the experimental protocol.3.Statistical analysis of the main variables: Analyze the data of the full analysis set and the matching plan set.

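### Section 4.4 leaves open whether lipid-lowering drugs are continued or newly given, and the lipid and CRP outcomes are analysed by unadjusted and paired t tests that ignore this

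*Protocol article*

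**What the plan says.** All references are to the protocol article.

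- **Section 4.4, Groups, background drugs.** The text reads "Their basic treatment can maintain the original plan, which includes a hypoglycemic regimen comprising acarbose + insulin detemir", and the same sentence goes on to antihypertensive drugs. A separate sentence follows: "Following which lipid-lowering drugs like atorvastatin will be administered". It gives no start time and does not say which patients it covers.
- **Section 4.4, the two arms.** Background treatment is the same in both: "Control group: Basic treatment + Chinese medicine placebo" and "Treatment group: Basic treatment + Shenqi compound".
- **Section 4.5.3.** Participants may take no other drugs during the 8-week period.
- **Section 4.8.2.** Four lipid fractions and CRP are secondary outcomes: "HbA1c, inflammation indicators and blood lipid will be tested at visits 1 and 5". Section 4.9.2 places the lipid samples at baseline and week 8.
- **Section 4.9.1.** Before the trial starts, "a history of diabetes, current medication, other medical history, and treatment history will be recorded".
- **Section 4.9.8.** Measurement data are compared by t test. A "Paired design" t test may be used within groups. No baseline value or drug status enters either test.
- **Section 4.5.6 and the Discussion.** Participants and treating researchers are described as hard to blind, and the trial is called open label.

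**The concern.** The sentence on lipid-lowering drugs stands outside the list of drugs that are maintained, and it looks forward in time. It can be read as an instruction to start such a drug in patients who do not yet take one. Section 4.5.3 points the other way, and three hospitals could settle the matter differently.

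The co-treatment acts on the quantities that are measured. If some patients start a lipid drug between visits 1 and 5, the change in LDL-C becomes a mixture of a drug response and no response. Two things follow for the analysis in section 4.9.8:

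- the unadjusted between-arm test carries variance that a recorded baseline variable could partly remove;
- the paired test within the Shenqi arm measures Shenqi and the new lipid drug together.

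The Discussion treats the effect on blood lipids as something the trial must evaluate, so these outcomes will be interpreted.

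**Working it through.** **The plan's own figures.** The protocol gives no figure for lipids or CRP. Its only calculation is the sample size for SDBG in section 4.5.7: 2 × [(1.64 + 1.28) × 2.41 / 2.0]² = 24.76 per group. This reproduces and plays no part here.

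**Side by side.** Section 4.4 (maintain the plan, then administer lipid drugs) and section 4.5.3 (no other drugs for 8 weeks) agree only if the lipid drug is already part of basic treatment. If it is new between baseline and week 8, they conflict.

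**Loss of precision, LDL-C.** All inputs are assumptions:
- s, SD of change without a new drug: 0.5–0.7 mmol/L
- f, share starting: 0.3–0.5
- D, fall after starting: 0.8–1.3 mmol/L

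Variance ratio = [s² + f(1 − f)D²] / s². Information lost = 1 − 1/ratio.
- Smallest: (0.49 + 0.21 × 0.64) / 0.49 = 0.6244 / 0.49 = 1.27. Lost: 1 − 1/1.27 = 21%.
- Largest: (0.25 + 0.25 × 1.69) / 0.25 = 0.6725 / 0.25 = 2.69. Lost: 1 − 1/2.69 = 63%.

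The formula is for change scores. Section 4.9.8 does not say whether change or week 8 values are compared; for week 8 values the ratio could differ.

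**Error rates and power.** LDL-C change was simulated with 25 and 30 per arm, s = 0.6 and 0.8, and D = 0.5, 1.0 and 1.5 mmol/L. There were 20,000 trials per scenario, and 3,000 for the adjusted test. These inputs are also assumed.

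| Scenario | Test | Result |
|---|---|---|
| No Shenqi effect, equal start rates (30% or 50%) | Between arms, unadjusted | Type I error 4.7–5.3%, mean bias about 0 |
| Shenqi effect 0.5 mmol/L, no starts | Between arms, unadjusted | Power 60–90% |
| Shenqi effect 0.5 mmol/L, 50% start in each arm | Between arms, unadjusted | Power 35–84% |
| Same | Adjusted for starting | Power 58–89% |
| No Shenqi effect, starts 60% v 40% | Between arms, unadjusted | Bias 0.1–0.3 mmol/L, type I error 7–23% |
| Same | Adjusted for starting | Type I error 4.5–5.8% |
| No Shenqi effect, 30% start | Paired, within arm | Significant in 14–75% |
| No Shenqi effect, 50% start | Paired, within arm | Significant in 30–99% |

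The adjusted rows use actual starting. Drug use at visit 1 carries the same information only if every non-user starts and no user changes; otherwise it recovers less. No corresponding figures were derived for CRP, triglycerides, total cholesterol or HDL-C.

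**The case against.** **New starts are only one reading.** Section 4.4 may simply list lipid-lowering drugs as a third part of continued basic treatment, in awkward English. The sentence has no time anchor, and a start could fall in the 2-week screening period. Section 4.5.3 argues against new drugs. This stands: a reader might infer that on-study statin starts are planned, and the text does not establish that. What remains is that the passages do not settle the question.

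**The randomised comparison is not confounded.** A reader might infer that statin starts could mimic a Shenqi effect between arms. Basic treatment is common to both arms and allocation is random, so with equal start rates the type I error stays near 5%. Chance imbalance is real. With 18 or 30 of 60 patients not on a drug, the arms differ by 6 or more with probability 0.158 or 0.196, and a gap of 6/30 moves the LDL-C difference by 6/30 × D = 0.16–0.26 mmol/L. But this is the same noise already in the t test's standard error, not a second harm. Mimicry between arms needs start rates that differ by arm. Open-label conduct permits that, but no passage states it.

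**Covariates may sit in an analysis plan that is not shown.** This stands in part. An unadjusted t test in a randomised trial is valid, and the absence of a covariate from an article is not in itself an error. But section 4.9.8 does name its tests, and the paired test is among them.

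**The size is assumed.** This stands in full.

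**Conclusion.** The point holds in a limited form. Section 4.4 is unclear on whether lipid-lowering drugs are continued or newly given, and a new start would contradict section 4.5.3. If some patients do start on study, the unadjusted between-arm test of lipids and CRP loses precision, and the paired test can be significant without any Shenqi effect.

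For LDL-C the loss corresponds to a variance of change about 1.3 to 2.7 times larger. This rests on 30–50% starting and on assumed SDs and drug effects; the protocol supplies none of them. If nobody starts or changes a lipid drug, this loss does not arise.

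The documents do not support a claim that the between-arm results are biased or confounded. Only secondary outcomes are concerned; the ultrasound primary outcome and the SDBG sample size are not affected. The analysis change is an inexpensive improvement to a stated method, not the correction of an invalid test.

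**What to change.** 1. **Reconcile** the two sentences of section 4.4 with each other and with section 4.5.3, so that all sites read the same instruction on lipid-lowering drugs. Which instruction applies is for the investigators.
2. **In section 4.9.8**, compare total cholesterol, triglycerides, HDL-C, LDL-C and CRP between arms at visit 5 by ANCOVA. Use the visit 1 value and visit 1 lipid-lowering drug use (yes/no) as covariates, the latter taken from the current medication already recorded under section 4.9.1.
3. **Rest lipid and CRP conclusions on that comparison.** Within-group paired t tests may be shown as description only.
4. **Describe by arm** any lipid-drug start or change after visit 1. An analysis that leaves these patients out should be labelled exploratory, because it conditions on a post-randomisation event in an open-label trial.

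Cost: two degrees of freedom (58 become 56 with all 60 patients) and one line on the case report form at visit 5. Both covariates are already collected, and the sample size does not change.

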#### Traditional Chinese medicine intervention

4.5.3

All participants in the treatment group will visit the researchers once every month, when the same Chinese doctor will examine them using four TCM diagnostic methods including inspection, listening and smelling, inquiry, and pulse measurement and palpation. Shenqi compound is composed of 8 Chinese herbs: ginseng, astragalus, raw radix rehmanniae, trichosanthin, dogwood, yam, salvia, and wine rhubarb. Ginseng and astragalus supplement the vitality together as the remedy. The four medicines are used in cooperation with each other to supplement the deficiency of yin and jin of the lungs, spleens, and kidney. Salvia miltiorrhiza and wine rhubarb are used as adjuvants to promote blood circulation and remove blood stasis. Shenqi compound regulates the body's energy metabolism and reduces blood glucose fluctuation, which is a good recipe for clinical treatment of type 2 diabetes with lower extremity atherosclerosis. At present, it has been included in the “Diagnosis and Treatment Program for Diabetes” of the Chinese Traditional Medicine Clinical Research (Diabetes) Base. The test drug is a Chinese medicine formula granule produced by Sichuan Green Pharmaceutical Technology Development Co., Ltd. Certification and quality control by director of the department of pharmacy department in the Teaching hospital of Chengdu University of TCM. Usage instructions suggest consuming the granules three times a day one lattice each time, by boiling with water before meals, stirring, covering, and sealing for 3 to 5 min. The main ingredients of placebo are beta-cyclodextrin and artificial food colors. Shenqi compound and placebo are both fried-free granules, are similar in packaging, appearance, and shape. Participants are not allowed to take other drugs during the 8-week study period. Each participant will receive 28 boxes of Chinese medicine formula granules. Participants will be asked to record the changes in their symptoms daily using a form reviewed by a researcher once every month.

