#### Rejection criteria

4.6.5

1.Those who do not to meet either the inclusion or exclusion criteria after enrollment;2.Those who have not used the medicines according to the regulations, cannot judge the curative effect or provide incomplete information;3.Those who have consumed drugs that are forbidden and may influence the judgment of effection;4.Those who have acute infection during the test

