**Figure 1 F1:**
[figure not shown]
The schedule of visits and measurements.

Screening period: 2 weeks prior to the intervention. Intervention period: 8 weeks. Follow-up period: 24 weeks after the intervention.

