#### Blood samples

4.9.2

Blood samples will be collected after fasting overnight, including blood glucose levels (baseline, w4, w8), postprandial C peptide and glucose levels at 0.5, 1, 2, and 3 h (baseline, w8), along with HbA1c and blood lipid (baseline, w8). The kit is provided by Depp. Blood samples will be sent to the laboratory of Teaching Hospital of Chengdu University TCM for analysis.

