This study also has some limitations. First, the sample size is not large enough. Second, the 8-week treatment period and the 24-week follow-up period may slightly short. Further research can be carried out in the future for in-depth evaluation.

Summarily, this study provides the experimental basis for the clinical treatment of blood glucose fluctuation. The application of Chinese medicine Shenqi compound in type 2 diabetes with lower extremity atherosclerosis can obtain evidence-based medicine.

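### Section 4.4 doses the treatment arm for 4 weeks with 8 weeks of observation, but the abstract, timeline and limitations give 8 weeks of treatment and 24 of follow-up

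*Protocol article*

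**What the plan says.** Section 4.4 (Groups) describes the treatment arm as basic treatment plus Shenqi compound, one bag three times a day, "for a period of 4 weeks. Followed by observation for 8 weeks". No duration is given there for the placebo arm.

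Three other places state both the treatment and the follow-up length, and they agree with each other:

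- Abstract, Methods: "32-week study period (8 weeks for intervention and 24 weeks for follow-up".
- Section 4.7.1, text under Figure 1: "Intervention period: 8 weeks. Follow-up period: 24 weeks after the intervention".
- Discussion, limitations: "the 8-week treatment period and the 24-week follow-up period may slightly short".

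Two further sections fit an 8-week course without giving a follow-up length. Section 4.5.3 says "Participants are not allowed to take other drugs during the 8-week study period". Section 4.9.2 takes fasting glucose at baseline, w4 and w8, the postprandial glucose and C-peptide series at baseline and w8, "along with HbA1c and blood lipid (baseline, w8".

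**The concern.** The length of treatment is part of the definition of the intervention, and the article gives two incompatible values for it. The other usage statements (sections 4.5.3 and 4.10.2) give dose and preparation but no length. Staff at any of the three hospitals who look up how long to dose would find 4 weeks in section 4.4 and 8 weeks in the timeline.

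Three things are at stake:

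- **Exposure.** The tested course could be half as long as intended, or could differ between sites.
- **Meaning of the week-8 data.** The same sample is an end-of-treatment value under one schedule and an off-drug value under the other. The w4 glucose value likewise changes from mid-treatment to end of treatment.
- **Analysis sets.** The full analysis set rule in section 4.9.8 says "If the case fails to complete the treatment course, the final observation should be implemented instead". The rejection criteria in section 4.6.5 remove "Those who have not used the medicines according to the regulations". The per-protocol set requires adherence to the treatment protocol. All three depend on how long the course is.

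**Working it through.** **Inputs.** Section 4.4: 4 weeks of drug, then 8 weeks of observation. Abstract, section 4.7.1 and limitations: 8 weeks, then 24 weeks. Dose: three bags a day (sections 4.4 and 4.10.2). Supply: 28 boxes per participant (section 4.5.3), with bags per box not stated.

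**Step 1: reproduce the stated total.** Treatment plus follow-up = 8 + 24 = 32 weeks, which is the abstract's figure. Section 4.4 gives 4 + 8 = 12 weeks, which matches no total in the article. The last anthropometric time point in section 4.9.1, w24, also lies beyond 12 weeks.

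**Step 2: date visit 5.** Section 4.8.2 tests blood glucose at visits 1, 3 and 5. Section 4.9.2 takes it at baseline, w4 and w8. Matching the two lists in order puts visit 5 at w8. The β-cell indices, HbA1c, lipids and inflammation markers (section 4.8.2) and the safety indexes (section 4.8.4) are all tested at visits 1 and 5, hence at baseline and w8.

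**Step 3: compare the schedules.** Doses = 3 × 7 × weeks of treatment.

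| Quantity | Section 4.4 | Abstract, 4.7.1, limitations |
|---|---|---|
| Weeks of treatment | 4 | 8 |
| Doses per participant | 3 × 28 = 84 | 3 × 56 = 168 |
| Weeks observed after treatment | 8 | 24 |
| Total weeks | 12 | 32 |
| Weeks off drug at w8 | 8 − 4 = 4 | 8 − 8 = 0 |
| Bags per box if 28 boxes last the course | 84 / 28 = 3 | 168 / 28 = 6 |

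The exposure ratio is 84 / 168 = 0.50.

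**Step 4: effect on safety.** The laboratory tests and ECG in section 4.8.4 are scheduled only at visits 1 and 5. Under section 4.4 none of them after baseline would fall during dosing or at its end. An abnormality that resolved within 4 weeks of stopping could go unseen.

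**Step 5: effect on completion.** A participant who stops the drug at day 28 has finished the course under section 4.4. Under the 8-week plan the same participant has not, and falls under the last-observation rule, the rejection criterion on medicine use, and possible exclusion from the per-protocol set.

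**The case against.** The strongest reply is that the intended schedule is not in doubt. The abstract, the dedicated timeline and the limitations agree, the 32-week sum works, and the sampling times fit an 8-week course. On that view section 4.4 is a slip for copy-editing. The sample size and analysis methods are untouched, and nothing shows that sites would follow section 4.4 over the timeline. It is correct that the intention can be inferred and that the consequences are conditional on sites following the section. But section 4.4 is the only dosing instruction with a duration, so it is the sentence a site would naturally act on.

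Four narrower points have some force:

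- The full 8-plus-24 pair appears in three places only. Section 4.5.3 gives just 8 weeks and calls that the study period. The list in section 4.9.1 ends at w24, short of w32 if counted from baseline. Neither states a competing pair of treatment and follow-up lengths.
- The 28-box supply does not decide the matter. Three bags per box fits 4 weeks and six fits 8 weeks.
- The article sets no explicit day-28 or day-56 threshold for completion. The effect on the analysis sets is an inference from rules that refer to the treatment course or the treatment protocol.
- The w8 date for the inflammation markers is inferred from visit numbering, and the visit schedule figure is not shown.

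These limit how far the consequences can be pressed. None of them reconciles the two schedules.

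**Conclusion.** The concern holds: section 4.4 is wrong as written and must be corrected. Every other place that states both the treatment and follow-up lengths gives 8 and 24 weeks, and only that pair yields the stated 32 weeks. Followed literally, section 4.4 gives 50% of the intended exposure (84 against 168 doses), cuts post-treatment observation from 24 weeks to 8, and moves the w8 secondary efficacy and safety measurements from end of treatment to 4 weeks off drug.

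This rests on two readings: that the 4 and 8 weeks in section 4.4 run one after the other, as its wording indicates, and that visit 5 is w8. Visit 8 is undated in the text shown, so no conclusion is drawn for the primary ultrasound outcome.

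**What to change.** Amend section 4.4 to say that participants in both arms take the study granules (Shenqi compound or placebo) for 8 weeks and are then followed for 24 weeks, in line with the abstract, section 4.7.1 and the limitations.

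At the same time, confirm that the 28 boxes in section 4.5.3 cover 56 days at three bags a day, which is 168 bags or 6 per box. If a box holds only 3 bags, the supply covers 28 days and must be doubled.

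The text change is one sentence, with no cost to sample size or analysis. The only possible material cost is extra drug and placebo if the supply check fails.
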